### Intervention channel: smartphone app

Mothers randomly assigned to the intervention group will download the app. It will be available free of charge on Android-based and Google Play. This app fills in one’s gestational age, expected delivery date, basic information about the disease, exercise amount, and dietary pattern during registration. By pushing a message through this app, one can acquire health information and promote one’s own health behavior. The study participants will be received a message programmed to push notifications every day. The items configured in Table 2 were pushed as messages according to the pregnancy cycle. Mothers will receive the health information that is needed to check via push notifications or will be viewed by clicking on it.

Additionally, mothers will be required to access and engage the app on a daily basis. In particular, blood pressure, blood sugar, and weight were recorded. These daily records can provide a cautionary warning when risk levels are reached during pregnancy, which can prevent emergencies.

This app has five core functions.Mothers can record their blood sugar, blood pressure, and weight every day and check the changes through calendar images and self-manage whether the blood sugar, blood pressure, and weight can be managed at appropriate and maintain them at normal levels.The section on physical activity and exercise is made with evidence-based data as practical tips during pregnancy and is composed of image and video files for easier use. It consists of physical activities and exercises that can be performed in daily. Messages about participation and promotion will send twice a week to prevent fatigue by pushing the same content.Comprehensive guidelines for weight, nutrition, and diet during pregnancy have been formulated based on evidence-based data. A more suitable dietary pattern and nutritional diet will be provided based on the first dietary pattern recorded by the person.A validated Edinburgh Depression Test Sheet was used for prenatal-postpartum depression. Mothers will be guided to re-test once every two weeks, and a notification will appear so that you can check the mother’s mood and emotions once a week. Additionally, questionnaires about anxiety, maternal–fetal attachment, self-esteem, social support, and traumatic experience in high-risk pregnancies were provided so that more specific psychological states will be identified.One can make a self-record. Mothers can self-record their condition during pregnancy. Previous research has showed that self-recording can promote changes in one’s own behavior and self-esteem and that it helps reduce physical symptoms, such as blood pressure.

The smartphone app key features are to enable mothers in acquiring the pregnancy’s health care information, showing that high-risk mothers can change into healthy mothers with better behaviors towards health. The main functions of this app were prepared based on evidence from various overseas guidelines and literature data and were confirmed by obstetricians, gynecologists, and expert councils to suit the characteristics of high-risk mothers. In addition, clinical psychologists and preventive medicine scientists, including app design companies, presented opinions on establishing detailed data. In addition, the usage, main functions, and each item of the participant’s app users will be recorded and quantified when the study is completed.

### Outcome measure

Table 3 shows the intervention and control groups measured item results, and the same items will be measured after the 6-week study participation period. Primary measurements will include weight, blood pressure, blood sugar and health literacy, and physical and obstetric characteristics. In addition, character, exercise and nutritional information on basic demographic characteristics and basic psychological state will be collected. For the primary measurement, the same information will be collected for both the primary and final results for comparison with the final result.

**Table 3 Tab3:** Outcome measure items

1	Weight, blood pressure, blood sugar measurement
2	Health information literacy
3	Physical and obstetric characteristics (including height, weight, gestational age, date of birth, etc.)
4	Basic demographic characteristics (spouse, marital status, economic status, etc.)
5	Basic psychological status (prenatal-postpartum depression questionnaire, high-risk-related trauma questionnaire, anxiety, and psychological state)
6	International Physical Activity and Exercise Questionnaire (IPAQ)
7	Nutrition and Dietary Questionnaire
8	Newborn information data (weight, head circumference, pregnancy method, birth period, etc.) (after 6 weeks/in case of delivery)
9	Questions for high-risk mothers
10	Smartphone app evaluation questionnaire (only intervention group)
11	App usage effect confirmation questionnaire (only intervention group)
12	Self-report (only intervention group)

Items 1 to 9 in Table 3 are for the intervention and control groups measurement. Item 1 measures body weight, blood pressure, and blood sugar daily during the study period. The amount of change from the start to the end of the study will be evaluated. Item 9 is about high-risk mothers and asks them to check for the diseases that apply to them, such as gestational hypertension, gestational diabetes, and prenatal-postpartum depression. This item will be completed at the beginning and end of the study. When the study is over, it will also be checked whether the disease is maintained. This can help with the prevalence and maintenance of healthcare-related diseases.

On the other hand, to check changes in health behaviors, the International Physical Activity Questionnaire (IPAQ) [26] is used to evaluate changes in health behaviors with a questionnaire verified in the pregnancy cohort. In addition, the results of maternal nutrition and diet measure the change in health behavior toward diet and nutrition by comparing before and after the mother’s recorded eating habits and nutrition and dietary behavior questionnaires.

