### Enrollment and eligibility

This study will be conducted at the Department of Obstetrics and Gynecology and Public Medical Center of Gachon University Gil Hospital in South Korea. This hospital is affiliated with the university and is in charge of medical care for the entire pregnancy cycle. Women aged ≥ 18 years who were diagnosed with gestational diabetes, gestational hypertension, and depression during or after pregnancy will recruit if they own a smartphone.

Participants selected by the medical staff will be admitted to the hospital. After that, you will be informed of consent and explanation for participation in the study by the research staff. Written or verbal informed consent will be obtained from all participants. Personal and demographic information, including contact information, will be collected. Also, On the consent form, participants will be asked if they agree to use of their data should they choose to withdraw from the trial. Participants will also be asked for permission for the research team to share relevant data with people from the Universities taking part in the research or from regulatory authorities, where relevant. This trial does not involve collecting biological specimens for storage. Upon randomization, participants will be categorized into two groups (intervention and control groups). Next, all participants will receive a Bluetooth weighing machine, blood pressure machine, and wearable blood glucose machine.

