## Discussion

This randomized controlled trial aimed to change the health behavior of high-risk mothers by providing health care information services through the development of a smartphone app. This research can be said to be the safest and most suitable research in the present, where smart medical technology is considered more important than mHealth technology. In addition, a smartphone app can be used by anyone and anywhere, promoting a healthier and more adaptive life and playing a big role in preventing diseases.

Therefore, this study will significantly help mothers and newborns in maintaining a healthy life during and after pregnancy. In addition, if this app is used properly in actual clinical sites and the general community, this smartphone app is expected to play a very useful role for medical staff. The accumulated information acquired through this app can be of help to medical staff in determining more efficient diagnosis and treatment management, which can contribute to the formation of medical artificial intelligence algorithms.

However, considering that the actual clinical setting or the characteristics of a high-risk mother are a more complicated process through various situations and changing physical conditions, this smartphone app will not replace the medical staff in the actual field. Nevertheless, there is no doubt that this app will be a great tool for medical staff, guardians, and patients to collaborate by playing an auxiliary role in a healthy life and prevention of disease via innovative medical technology. In the future, it will be necessary to establish a continuous algorithm through collaboration between obstetricians and gynecologists, preventive medicine, psychologists, and IT experts, and to discuss the direction of use and connection of smart medical technology. In addition, smartphone-based apps using the currently configured items will require clinical verification through various studies, including actual clinical studies, to secure external validity in the future [27]. Therefore, empirical research or analysis of this smartphone application should be conducted in follow-up studies.

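### The measurements called primary do not match the behaviour-change aim, and no single primary endpoint is fixed for a mixed population that may deliver during the 6 weeks

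*Protocol article*

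**What the plan says.** **What is called primary.** Outcome measure, protocol article: "Primary measurements will include weight, blood pressure, blood sugar and health literacy, and physical and obstetric characteristics". The wording leaves the list open. Table 3 item 3 describes the last entry as including height, weight, gestational age and date of birth, so weight appears twice. The next step is that "the same information will be collected for both the primary and final results for comparison with the final result".

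**What the aim is.** The main Discussion says: "This randomized controlled trial aimed to change the health behavior of high-risk mothers". The end of Outcome measure assigns behaviour change to the IPAQ and the nutrition and diet questionnaires. Statistical analysis treats behaviour change as the end point that its regressions are to explain. Neither questionnaire is on the primary list; exercise and nutrition are collected in addition to it.

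**Who is measured, and how.** Women are eligible if "diagnosed with gestational diabetes, gestational hypertension, and depression during or after pregnancy" and owning a smartphone. Item 9 "asks them to check for the diseases that apply to them, such as gestational hypertension, gestational diabetes, and prenatal-postpartum depression", so diagnoses differ between women. There is no restriction by condition: "Items 1 to 9 in Table 3 are for the intervention and control groups measurement". For daily weight, blood pressure and blood sugar, "The amount of change from the start to the end of the study will be evaluated". Item 8 provides for newborn data when delivery occurs.

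**How the results will be used.** Sample size calls the study exploratory, with no hypothesis test. Objectives, and the abstract's own discussion, speak of showing that the app is effective.

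**The concern.** A reader cannot tell which result decides whether the app worked. The list called primary holds clinical values, a literacy score and fixed traits that no app can change. The behaviour measures that carry the stated aim are outside it. If effectiveness is later claimed, the measure with the best result could be put forward.

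The clinical measures also fit the population poorly. A blood sugar comparison includes women enrolled for depression or hypertension, and a blood pressure comparison includes women without hypertension. A plain start-to-end weight change mixes women who stay pregnant with women who give birth in between. The headline result could be ambiguous and noisier than it needs to be.

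**Working it through.** **1. The plan's own figures.** None rests on an outcome. The documents give no significance level, power, effect size, SD, diagnosis mix or share delivering. The one step that can be reproduced, 300 × (1 − 0.5) = 150, concerns 12-month retention. The calculations below are therefore scenarios, with two-sided 5% assumed.

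**2. The sections side by side.**

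| Section | What it treats as the key result |
|---|---|
| Outcome measure, opening | Weight, blood pressure, blood sugar, literacy, physical and obstetric traits |
| Outcome measure, end | IPAQ and diet, as the behaviour measures |
| Statistical analysis | Behaviour change; tests tied to no named outcome |
| Discussion | Behaviour change |

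The first row conflicts with the other three. If 'primary' is read as 'first', the conflict goes, but so does any named primary endpoint.

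**3. Several chances of success.** For k independent tests, the chance of at least one false positive is 1 − 0.95^k.
- k = 4 (weight, blood pressure, blood sugar, literacy): 1 − 0.95^4 = 18.6%
- k = 5 (systolic and diastolic counted separately): 1 − 0.95^5 = 22.6%

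Correlation between measures, as between systolic and diastolic pressure, lowers both figures.

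**4. Averaging over unaffected women (blood sugar and blood pressure only).** Let f be the share with the matching condition, and assume no response in the others. The average effect becomes f × d. Relative to a trial in which every woman is affected, the total needed is 1/f² when pooled and 1/f when only affected women are analysed.
- f = 1/2: 4 times against 2 times
- f = 1/3: 9 times against 3 times

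Power at an assumed effect of d = 0.4 SD in affected women:

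| f | 250 evaluable, pooled | 250, affected only | 500 evaluable, pooled | 500, affected only |
|---|---|---|---|---|
| 0.67 | 56% | 74% | 85% | 96% |
| 0.50 | 35% | 61% | 61% | 89% |
| 0.33 | 18% | 44% | 31% | 73% |

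The 250 is 500 × 0.5. It borrows the plan's 12-month dropout rate, so at 6 weeks it is a pessimistic assumption.

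**5. Delivery inside the window (weight).** If a share q delivers and delivery shifts weight change by D, the variance rises by q(1 − q)D². Assume an SD of 2 kg otherwise (variance 4), D of 5 to 7 kg, and entry spread evenly over weeks 24 to 40 with birth at week 40, so that q = 6/16, about 0.38.
- D = 5: 0.38 × 0.62 × 25 = 5.9; SD = √9.9 = 3.1 kg; 9.9/4 = 2.5 times the women
- D = 7: 0.38 × 0.62 × 49 = 11.5; SD = √15.5 = 3.9 kg; 15.5/4 = 3.9 times the women

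Women enrolled after birth cannot deliver, which lowers q. At q = 0.10 the added variance is 0.09 × 25 = 2.25 or 0.09 × 49 = 4.41, giving 6.25/4 = 1.6 or 8.41/4 = 2.1 times the women.

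**The case against.** **'Primary' may mean the first measurement.** Outcome measure sets it against the final result, and Statistical analysis speaks of the first and the final outcome. This would explain why height and date of birth are listed. It is a fair reading, and it means the text does not establish five co-primary endpoints. It does not remove the problem, because an outcome section would then name no primary endpoint.

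**The study is called exploratory.** That limits the error rates in step 3: they matter only if effectiveness is claimed. Objectives and the abstract do intend that claim.

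**Not every measure is diluted.** A reader might infer that all of them are. Health literacy is not tied to a diagnosis, and weight is not an enrolling condition. Nor do the documents show that most women cannot respond: no diagnosis mix is given, women may have several conditions, and the app also aims to keep values normal and prevent disease. The multipliers in step 4 are illustrations.

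**Delivery does not bias the comparison.** A reader might infer bias, but 1:1 randomisation balances delivery between arms in expectation. Daily readings also mean that values before delivery exist.

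**Postpartum enrolment is not fully clear.** The phrase about timing in "diagnosed with gestational diabetes, gestational hypertension, and depression during or after pregnancy will recruit if they own a smartphone" may attach only to depression, and app registration asks for an expected delivery date. Even so, women with postpartum depression would be enrolled. The same sentence, read literally, requires all three diagnoses at once; item 9 shows that this is not meant.

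**Analysis sets, covariates and strata may sit in a fuller document.** That is accepted. Their absence from an article is not a fault, and they appear below only as part of the remedy.

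**Conclusion.** The point holds in this form. The measurements called primary and the stated behaviour-change aim do not agree, and on either reading of 'primary' no single endpoint is fixed. This conclusion needs no assumption.

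The sizes do rest on assumptions:
- 18.6% to 22.6% for at least one false positive, given independent tests at 5% and an effectiveness claim.
- 4 against 2 times the women at f = 1/2, or 9 against 3 times at f = 1/3, for blood sugar and blood pressure only, given no response in unaffected women.
- 2.5 to 3.9 times the women for weight change at 38% delivering, and less if postpartum women are enrolled. This is a loss of precision.

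The trial can run as designed, but the ambiguity should be removed before it starts. Trial status says it has not begun.

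**What to change.** **(a) One primary measure.** Reconcile Outcome measure with Statistical analysis by naming one measure at 6 weeks that applies to every woman and matches the aim: IPAQ activity or the diet score. Both are already collected in both arms (Table 3 items 6 and 7). Make the rest secondary, reported with confidence intervals. Treat height, dates and demographics as baseline data.

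**(b) Condition-specific reporting.** Report blood sugar in women with gestational diabetes at entry and blood pressure in women with gestational hypertension at entry. Give the all-women result as supportive.

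**(c) Adjustment.** Adjust the between-arm models for baseline value, entry diagnosis, pregnant or postpartum status and, for women pregnant at entry, gestational age. For weight change, add a supportive analysis of the daily readings up to delivery.

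**Cost.** The change is to wording, with no new data. The clinical measures lose primary status, and their condition-specific estimates come from smaller subsets: in the scenario above, 44% power at f = 0.33 with 250 evaluable, which is still better than 18% pooled. Keep the randomisation strata few. Crossing all seven combinations of three diagnoses with pregnant or postpartum status would give 7 × 2 = 14 strata, and this is not needed when the models adjust for these factors.

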### Statistical analysis

This study will compare the outcomes between the two groups using IBM SPSS software for statistical analysis. For this purpose, descriptive statistics and correlation analysis of each group are performed, and a paired sample T-TEST of two groups is performed, so that comparative analysis can be performed. In addition, pre-post-group comparison analysis will be conducted, especially for both groups, from the first outcome to the final outcome. Hierarchical and stepwise regression analyzes will be conducted to determine the impact of each item to look at changes in health behavior as the end result.

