## Methods/design

### Objectives

The overall goal of this trial is to target the effectiveness of a smartphone app for health care interventions in high-risk mothers. Providing healthcare interventions via a smartphone app demonstrates the effectiveness of smart medical technology. Therefore, in this study, more specifically, the study group using the app and the group using paper health management information will compare over a period of 6 weeks.

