### Study design

This study will be conducted in accordance with SPIRIT’s clinical trial protocol guidelines. This study will be conducted as a clinical trial study according to the following framework and will compare the two groups. This randomized controlled trial (two-armed RCT) will be conducted for 6 weeks to provide healthcare service information based on a smartphone app for high-risk mothers during their entire pregnancy. A diagram of the study design is shown in Fig. 1. In addition, based on the research design, the procedure for developing a mobile app using the IDEAS framework [17] was followed, which is an appropriate procedure to lead to healthy and positive outcomes through the development of mobile digital medical interventions. The procedure is as follows [18] (Table 1):

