### Allocation of participants

The participants will be randomly assigned in the intervention group applying the app and the general control group providing the paper guidelines performed using computer-generated assignments in a 1:1 ratio. Considering the characteristics of the intervention, both the participants and researchers will aware of the group to which they will be assigned. In addition, this study will be conducted as a stratified block. Accordingly, the registration of participants and the assignment of interventions will be performed by the medical staff, and a random number table will be generated through a computer program to assign and enroll participants in the study.

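### The test named for comparing app with paper is a paired t-test, which measures change within an arm and not the difference between two independent randomised arms

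*Protocol article*

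**What the plan says.** All of this is in the protocol article.

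- **Objectives:** "the study group using the app and the group using paper health management information will compare over a period of 6 weeks".
- **Study design:** a two-armed randomised trial that "will be conducted as a clinical trial study according to the following framework and will compare the two groups".
- **Allocation of participants:** assignment is "performed using computer-generated assignments in a 1:1 ratio", and "this study will be conducted as a stratified block". No matching or pairing of women is described.
- **Statistical analysis:** the section opens with "This study will compare the outcomes between the two groups using IBM SPSS software for statistical analysis". To that end it lists descriptive statistics and correlations for each group, and then "a paired sample T-TEST of two groups is performed, so that comparative analysis can be performed". It adds that "pre-post-group comparison analysis will be conducted, especially for both groups, from the first outcome to the final outcome". Finally, "Hierarchical and stepwise regression analyzes will be conducted to determine the impact of each item", with change in health behaviour as the end result.
- **Sample size:** the study is described as exploratory and not as a test of a statistical hypothesis.

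The section names no independent-samples test, covariance model, arm-by-time model or other estimate of the difference between arms.

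**The concern.** A paired t-test needs two measurements on the same unit or on matched units. The women in the app arm and those in the paper arm are different people with no link between them. The workable reading is therefore start versus end of study within each arm, and that estimates change over time. Weight, blood pressure, blood sugar and mood can all move over 6 weeks of pregnancy or the postpartum period whichever material a woman receives. Women enrolled because of a high-risk diagnosis may also drift back towards their usual level. The control arm is there to remove these influences, and a within-arm test does not use it.

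At stake is the trial's own question. If the section is followed as written, the report would hold two tests of change and no app-minus-paper estimate with a confidence interval.

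**Working it through.** **Step 1. Match each named analysis to the objective.**

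| Analysis in the section | What it estimates | App minus paper? |
|---|---|---|
| Descriptive statistics and correlations per group | Summaries within an arm | No |
| Paired-sample t-test | Mean change within an arm | No |
| Pre-post comparison for both groups | On its plain reading, change within each arm | No |
| Hierarchical and stepwise regression | Contribution of each item to health-behaviour change | Only if an arm term is included; none is stated |

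**Step 2. Read the paired test literally, as app women against paper women.** The design supplies no pairs, so any pairing would be arbitrary. Simulating two independent normal samples with no difference (10,000 runs) gave type I error of 0.052 at 125 per arm and 0.051 at 250. This reading does not inflate the error rate. It does need equal numbers in the two arms, and its result depends on the order in which women happen to be listed.

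**Step 3. Illustrate the within-arm reading.**

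Inputs:
- Total 500 at 1:1 (Sample size; Allocation of participants), so 500 / 2 = 250 per arm with no loss.
- The only dropout figure is about 50%, given for 12-month data. It reproduces the article's recruitment number: 150 / (1 − 0.5) = 300. Applied to 500 it gives 500 × 0.5 / 2 = 125 per arm. No 6-week dropout is stated, so 125 to 250 is used as a range.
- Assumed, because the article gives none of these: no app effect; the same true mean change c in both arms, in SDs of the change score; two-sided 0.05 in each arm.

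Formulas: within-arm power p = P(|T| > t at 0.975, n − 1 df), where T is noncentral t with n − 1 df and noncentrality c√n. The arms are independent, so P(app arm only significant) = p(1 − p) and P(both significant) = p².

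Worked case, n = 125 and c = 0.20: noncentrality = 0.20 × √125 = 2.236 and p = 0.602. App only = 0.602 × 0.398 = 0.240. Both = 0.602² = 0.36.

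| c (SD of change) | n = 125: p | app only | both | n = 250: p | app only | both |
|---|---|---|---|---|---|---|
| 0.10 | 0.199 | 0.16 | 0.04 | 0.350 | 0.23 | 0.12 |
| 0.15 | 0.384 | 0.24 | 0.15 | 0.656 | 0.23 | 0.43 |
| 0.20 | 0.602 | 0.24 | 0.36 | 0.883 | 0.10 | 0.78 |
| 0.25 | 0.792 | 0.16 | 0.63 | 0.976 | 0.02 | 0.95 |
| 0.30 | 0.914 | 0.08 | 0.84 | 0.997 | 0.003 | 0.99 |

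A valid two-sided 0.05 test of the arm difference would favour the app in 0.025 of such trials, whatever c is. The app-only figure cannot exceed 0.25, its value at p = 0.5. At c = 0.50 both arms are significant almost always, still with no app effect.

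**The case against.** **The wording may be loose, and the detail may sit in an analysis plan.** An independent-samples test may have been meant, and the pre-post phrase could be read as pre-post by group. But this is not an omission. The article names a method for the between-group comparison and that method does not fit, so the sentence needs correcting whatever was intended.

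**The regressions could carry the comparison.** They could in principle, and it would be wrong to say that the paired and pre-post tests are the only analyses planned. Their stated purpose, however, is the impact of each item, and no arm term is named.

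**The study is exploratory.** This bears on how the harm is described. A reader might infer that significance in the app arm alone will be declared a benefit, or that the trial has a false-positive rate of 24%. The documents support neither. No such decision rule is stated, and 0.24 is close to the maximum of a figure that falls to 0.003 within the range shown. The exploratory label still does not supply the between-group estimate that the objective and the analysis section promise.

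**The 50% dropout belongs to 12-month data.** Correct, which is why 125 per arm is only one end of the range.

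**ANCOVA is not the only cure.** Also correct. An independent-samples comparison of change would test the right contrast too, and would suit the Outcome measure section, which speaks of change from start to end.

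**Conclusion.** The analysis is wrong as written. For the between-group comparison, the section names a test that addresses change within an arm, and nothing else in it is stated to estimate app minus paper. This conclusion rests on the text alone and needs no numerical assumption.

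The figures show only what could follow if the within-arm results were set against each other. With no app effect, the app arm alone would be significant with probability 0.08 to 0.24 at 125 per arm and 0.003 to 0.23 at 250 per arm, for a common change of 0.10 to 0.30 SD of change. Where that probability is small, it is because both arms are nearly always significant. Either pattern reflects time and not the app, and its frequency depends on a trend that the plan does not know.

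**What to change.** In the Statistical analysis section, replace the paired t-test as the comparative analysis:

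- **Continuous outcomes:** a between-arm analysis, such as ANCOVA of the 6-week value on randomised arm, baseline value and the stratification factors used in the allocation. Analyse women in the arm to which they were randomised. Report the arm difference with its 95% CI.
- **Disease maintained (yes/no):** logistic regression on arm and strata among women who had that disease at baseline. Omit a baseline-status term, because it is constant in that subset.
- **Within-arm pre-post changes:** keep as descriptive tables.

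The cost is wording in the analysis section only. The Outcome measure section already has the same items collected at start and end in both arms, and SPSS fits these models. The article does not name the strata, so they must be taken from the randomisation specification when the model is written. The Trial status section says the trial has not yet started, so the change can be made before any data exist.

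### The only test named for comparing the app and paper groups is a paired-sample t-test, which does not fit two independently randomised, unmatched arms

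*Protocol article*

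**What the plan says.** The Objectives section of the protocol article poses a between-arm question: "the study group using the app and the group using paper health management information will compare over a period of 6 weeks". Study design confirms the structure ("This randomized controlled trial (two-armed RCT) will be conducted for 6 weeks"), and Allocation of participants says that assignment is "performed using computer-generated assignments in a 1:1 ratio", in stratified blocks. No matching of individual women is described.

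The Statistical analysis section opens with the same aim: "This study will compare the outcomes between the two groups using IBM SPSS software for statistical analysis". To meet that aim it lists descriptive statistics and correlation analysis for each group, and then says that "a paired sample T-TEST of two groups is performed, so that comparative analysis can be performed". It adds that "pre-post-group comparison analysis will be conducted, especially for both groups, from the first outcome to the final outcome", without naming a method. It closes with hierarchical and stepwise regressions on the impact of each item, with no term for randomised arm stated.

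The Outcome measure section evaluates item 1 (weight, blood pressure, blood sugar) as the amount of change from start to end of the study. For diet it plans to "measure the change in health behavior toward diet and nutrition by comparing before and after".

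**The concern.** A paired t-test needs two linked readings, normally on the same person. Two randomised arms of different women have no such link, so the named test can be carried out in only two ways.

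- **Within each arm.** Each woman's final reading is paired with her first. The null hypothesis is then no change over 6 weeks in that arm, which is not the question in the Objectives. The natural shortcut is to contrast a significant app arm with a non-significant paper arm, and that is not a test of the difference.
- **Across arms.** Women are paired by their position in the data file. The design gives no basis for these pairs.

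The first reading matters most because change without any app effect is plausible. Women are enrolled during or after pregnancy, and weight, blood pressure and blood sugar can move over 6 weeks in both arms. The control arm is there to remove that shared movement, and a within-arm test does not use it for that. What is at stake is the trial's central comparison.

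**Working it through.** **Inputs.** From the article: two unmatched arms, 1:1, 500 women in total, hence 500 / 2 = 250 per arm. The article gives no significance level, effect size or standard deviation, so these are assumptions: two-sided 5%, normally distributed changes, no app effect, and the same true change *d* in both arms, in units of the SD of change. 125 per arm (half of 250) is a sensitivity value. The plan has no figure of its own to reproduce on this point.

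**Within-arm reading.** The probability that the app arm is significant is the power of a one-sample t-test on the changes:

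p = P(|T| > t_crit), where T is noncentral t with n − 1 df and noncentrality d√n.

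- n = 250, d = 0.2: d√n = 3.162, t_crit = 1.970, p = 0.883.
- n = 125, d = 0.2: d√n = 2.236, t_crit = 1.979, p = 0.602.

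The arms are independent, so the probability that the app arm is significant and the paper arm is not equals p(1 − p):

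- n = 250: 0.883 × 0.117 = 0.103.
- n = 125: 0.602 × 0.398 = 0.240.

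The product p(1 − p) cannot exceed 0.25, reached at p = 0.5. The result varies strongly with *d*:

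| Common change d | p, 250 per arm | App only, 250 | p, 125 per arm | App only, 125 |
|---|---|---|---|---|
| 0.1 | 0.350 | 0.228 | 0.199 | 0.159 |
| 0.2 | 0.883 | 0.103 | 0.602 | 0.240 |
| 0.3 | 0.997 | 0.003 | 0.914 | 0.078 |

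A between-arm test at two-sided 5% favours the app in 2.5% of such trials. Simulation (10,000 trials per setting) agrees: the independent-samples test rejected, in either direction, in 4.6% to 5.3% of trials in every setting.

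**Across-arm reading.** With arbitrary pairs, the mean of the paired differences equals the difference in arm means, and the expected covariance within a pair is zero. The null hypothesis is therefore still the between-arm one and the standard error is about right. In 20,000 simulated trials per setting, false positives were about 5% at 75, 125 and 250 per arm. Power for a true difference of 0.3 SD was within 0.5 percentage points of the independent test (about 44%, 66% and 92%).

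The fault here is arbitrariness. In one simulated data set of 75 per arm, 5,000 re-sortings moved the p-value between 0.003 and 0.055, while the independent test gave a single value of 0.022. Only 0.2% of the orderings crossed 0.05. When arm sizes differ, women without a partner are also dropped.

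**The case against.** The strongest reply is that the section does more than name one test. It states a between-group aim and provides per-group descriptive statistics, from which a difference can be formed. The pre-post-group comparison could be meant as a between-arm comparison of change, and the regressions could include arm. This stands in part. A reader might infer that the control arm goes unused or that the difference is never estimated, and the text does not support that. What remains is that none of these other analyses clearly specifies a valid between-arm test, and the one test named does not fit.

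A reader might also infer that the paired test has the wrong null hypothesis however it is run. That holds only for the within-arm reading; the across-arm reading keeps the between-arm null. The Outcome measure wording leans towards the within-arm reading but does not settle it, and the diet sentence describes measurement rather than a test.

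Three temptations on size should be resisted:

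- The 25% is a ceiling, reached only when single-arm power is 50%. With a large shared change both arms are significant and app-only significance almost vanishes; the risk is then that the app arm's change is read on its own.
- Regression to the mean cannot be sized from the article, because entry is by diagnosis and no reading threshold is given.
- The 50% dropout in the Sample size section concerns 12-month observation, so it does not make 125 per arm the expected number at 6 weeks.

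The Sample size section calls the study exploratory and not a test of a statistical hypothesis. That makes the 5% level an assumption of this check, but it does not make a paired test suitable for an aim that the article still states as comparing two groups. Nor is this detail left to an unseen analysis plan: the article names the method.

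**Conclusion.** The stated method is wrong as written. The article ties a paired-sample t-test to the comparison of two independently randomised, unmatched groups, and no other listed analysis clearly supplies a valid between-arm test.

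On the likelier, within-arm reading, with no app effect and a shared change of 0.2 SD, a significant app arm is expected in 88% of trials at 250 per arm and 60% at 125. A contrast of significant against non-significant would wrongly favour the app in 10% and 24%, instead of 2.5%. On the across-arm reading the error rate is acceptable, but the result depends on file order and data can be lost. The sizes rest on the assumed 5% level, normality and common change; the mismatch between test and design rests on none of them.

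**What to change.** In the Statistical analysis section, replace the paired t-test as the comparative analysis with a between-arm estimate and 95% confidence interval for each outcome:

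- **Continuous outcomes:** a linear model of the 6-week value with arm as the tested term, adjusted for the baseline value and for the factors used in the stratified allocation.
- **Yes/no outcomes, such as item 9 (disease present or maintained):** a between-arm comparison of proportions or a logistic model with arm as the tested term.

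Report within-arm pre-post changes, including diet and IPAQ, as descriptive only, and state that no app effect will be inferred from significance in one arm alone. If the pre-post-group comparison was meant as a between-arm comparison of change, say so and name the model.

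The cost is wording. No extra data or participants are needed, and the Trial status section says the trial has not started. The downside is that within-arm significant improvements can no longer be claimed as app effects.
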